**Table 1: measurement moments**

| Baseline (t0) | 1-2 months
(t1) | 3 months
(t2) | 6 months
(t3) | 9 months
(t4) | 12 months
(t5) | 18 months
(t6) | 24 months
(t7) |
|---------------|--------------------|------------------|------------------|------------------|-------------------|-------------------|-------------------|
| CRF-1  |                    | CRF-2     | CRF-3     | CRF-4     | CRF-5      | CRF-6      | CRF-6      |
| Visit 1       | Treatment          | Visit 2          | No visit         | No visit         | No visit          | No visit          | visit 3           |
| Randomization | APM or PT          |                  |                  |                  |                   |                   |                   |
| IKDC          |                    | IKDC             | IKDC             |                  | IKDC              |                   | IKDC              |
| RAND-36       |                    | RAND-36          | RAND-36          |                  | RAND-36           |                   | RAND-36           |
| EQ-5F5L       |                    | EQ-5D5L          | EQ-5D5L          | EQ-5D5L          | EQ-5D5L           | EQ-5D5L           | EQ-5D5L           |
| VAS           |                    | VAS              | VAS              |                  | VAS               |                   | VAS               |
| TAS           |                    | TAS              | TAS              |                  | TAS               |                   | TAS               |
| PSC           |                    | PSC              | PSC              |                  | PSC               |                   | PSC               |
| TiC-P         |                    | TiC-P            | TiC-P            | TiC-P            | TiC-P             | TiC-P             | TiC-P             |
| PSC           |                    | PSC              | PSC              |                  | PSC               |                   | PSC               |
| PE            |                    | PE               |                  |                  |                   |                   |                   |
| X-ray         |                    |                  |                  |                  |                   |                   | X-ray             |
| Expectation   |                    | Satisfaction     | Satisfaction     |                  | Satisfaction      |                   | Satisfaction      |
| MRI           |                    |                  |                  |                  |                   |                   |                   |

#### 8.4 Withdrawal of individual subjects

Participants are free to leave the study at any time for any reason if they wish to do so without any consequences. The investigator can also decide to withdraw a subject from the study for urgent medical reasons.

Participants who leave the study, will be considered as a drop-out and will be contacted in order to obtain information about the reasons for this and will be checked for any adverse events.

#### 8.5 Replacement of individual subjects after withdrawal

Patients will not be replaced after withdrawal.

#### 8.6 Follow-up of subjects withdrawn from treatment

Normal routinely follow-up at the outpatient clinic, standard control.

#### 8.7 Premature termination of the study

The criteria for terminating the study prematurely are a patient's wish at any time to discontinue treatment, any unforeseen/unrelated injury that occurs which would require a different treatment. The procedure, basically discontinuing the trial, will depend on the reason of termination. If allowed, we will continue to collect data on these patients according to intention-to-treat principles.

## 9. SAFETY REPORTING

### 9.1 Section 10 WMO event

In accordance to section 10, subsection 1, of the WMO, the investigator will inform the subjects and the reviewing accredited METC if anything occurs, on the basis of which it appears that the disadvantages of participation may be significantly greater than was foreseen in the research proposal. The study will be suspended pending further review by the accredited METC, except insofar as suspension would jeopardise the subjects' health. The investigator will take care that all subjects are kept informed.

### 9.2 Adverse and serious adverse events

Both treatment groups represent variations of standard treatment. We anticipate no treatment related risks related to participation in this study, but it is possible (though unlikely) that one treatment method will prove inferior to the other with respect to functional outcome.

Adverse events are defined as any undesirable experience occurring to a subject during the study. Adverse events are defined as any undesirable experience occurring to a subject during the study. All adverse events, other than pain and joint effusion which are normal findings after arthroscopic knee surgery, by the subject or observed by the investigator or his staff will be recorded.

A serious adverse event is any untoward medical occurrence or effect that at any dose:

- results in death;
- is life threatening (at the time of the event);
- requires hospitalization or prolongation of existing inpatients' hospitalization;
- results in persistent or significant disability or incapacity;
- is a new event of the trial likely to affect the safety of the subjects, such as an unexpected outcome of an adverse reaction, lack of efficacy of an IMP used for the treatment of a life threatening disease, major safety finding from a newly completed animal study, etc.

All SAEs will be reported through the web portal ToetsingOnline to the accredited METC that approved the protocol, according to the requirements of that METC.

SAEs that result in death or are life threatening should be reported expedited. The expedited reporting will occur not later than 7 days after the responsible investigator has first knowledge of the adverse reaction. This is for a preliminary report with another 8 days for completion of the report.

### 9.3 Suspected unexpected serious adverse reactions (SUSAR)

Not applicable.

**9.4 Follow-up of adverse events**

All adverse events will be followed until they have abated, or until a stable situation has been reached. Depending on the event, follow up may require additional tests or medical procedures as indicated, and/or referral to the general physician or a medical specialist.

**9.5 Data Safety Monitoring Board (DSMB)**

Not applicable.

## 10. STATISTICAL ANALYSIS

Data-analysis and presentation:

To investigate the effect of surgery, we will use generalized estimating equations (GEE) for longitudinal analysis in SPSS 18 on an intention-to-treat and per-protocol basis, as well as sub-group analysis of the cross-over patients. This method takes into account the dependency of observations within a patient, and the fact that not all patients may be assessed at each time point (missing data). In the primary GEE model, the outcome variable studied (e.g. physical function on the IKDC) will be analyzed as a dependent variable, using treatment allocation (1, intervention; 0, control) and time as a key independent variables. In the secondary GEE model, the outcome variables studied (e.g. general health on the RAND36, quality of life on the EQ5D-5L, level of activity on the TAS, knee pain on the question 10 of IKDC, the correlation between a patient's expectation and satisfaction, productivity losses on TiC-P, muscle strength, range of motion, squatting and adverse events) will be analyzed in a similar way. To evaluate whether the two groups differed in change over time the interaction term of group and time (group X time) will be assessed. Time will be included as a dummy variable (reference = baseline T0), and four interaction terms will be analyzed (T1Xgroup; T2x group; T3x group, T4x group). All models will be corrected for center of inclusion and age group. In additional analysis, we will investigate the possible confounding effect (defined as more than 10% change in the parameter estimate for groupXtime) of 5 variables (body mass index, gender, profession, ASA-classification, the affected meniscus, the type of tear and the stadium of OA according to the Kellgren Lawrence Grading Scale for Osteoarthritis).

At the following time points following the treatment (T2, T3, T5 and T7) we will describe the incidence of revisions (intervention group) or treatment failures (=delayed APM, control group) using descriptives. After two years (T7) we will compare the incidence of development or progression of OA between groups using a chi-squared test (or Fisher's Exact as appropriate). For all analysis, a two-tailed value of  $p < 0.05$  is considered to be significant.

In all models, missing data (intermittent/drop-out) will be analyzed on being missing completely at random (MCAR) or not (missing at random [MAR]). If not, each model will either be appropriately corrected or missings will be appropriately imputed (to be determined; e.g. last observation carries forward or multiple imputation). In the intention-to-treat analysis we already anticipate a 25% dropout which is non-ignorable (intervention related). Therefore, these data will be analyzed using a weighted GEE analysis. We will consult a statistician for all GEE analysis.

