### SECONDARY OUTCOMES:

#### 1) Change in:

- General health, measured by RAND-36;
- Quality of life, measured by EQ-5D5L;
- Pain, measured with the VAS both in rest and weight bearing;
- Level of activity, measured by Tegner Activity Scale (TAS);
- Patient specific complaints measured by the PSC (patient specific complaints) Questionnaire;
- Treatment group; number of patients initially treated conservatively, treated secondarily by APM.

We will use the EQ-5D5L to measure Quality Adjusted Life Years (QALY).

2) Productivity losses and the use of healthcare services, measured by a modified version of the Trimbos/iMTA questionnaire for Costs associated with Psychiatric Illness (TiC-P).

3) Relation between a participants expectation of treatment and their satisfaction.

4) Physical Examination (PE), consisting of performance on physical tests (squatting with duckwalk, Thessaly test, McMurray), the range of motion, joint line tenderness and the existence of joint effusion in the knee.

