### FOLLOW-UP:

Patients will visit the outpatient department for physical examination (3 months) and X-rays (24 months). All measurement outcomes will be obtained at baseline, 3, 6, 9, 12, 18 and 24 months, online or by hardcopy if preferable. Patients will be examined by a well experienced clinician at each site. The anticipated enrolment period will be approximately one year with follow up.

We also plan to perform another long-term outcome measurement after 5 years.

Endpoint: the first results of the study will be evaluated after 1 year of follow up. The endpoint for the primary outcome of the study will be after 2 years of follow up. However, we plan a follow up moment at 60 months to see the progression of osteoarthritis, measured with the Kellgren Lawrence Grading Scale for Osteoarthritis.

Sample size calculation:

Sample size is based on a power of 90%, an alpha of 0.05, a standard deviation of 18 points and a non-inferiority threshold of 8 points on the IKDC 'Subjective Knee Form'.

We calculated that with 10% loss to follow-up after 24 months and 25% delayed APM in PT group, 160 patients are needed per group in this equivalence type RCT. This means a total of 320 patients will be included. Sample size is calculated for the intention-to-treat analysis.

Assigning patients to treatment groups:

After signing and dating the informed consent form, patients will be randomized. This will be done in a web-based system, using the ALEA software, stratified for each site and for 2 age subgroups:

Subgroup 1: 45-57 years of age

Subgroup 2: 58-70 years of age

Patients who are excluded from the study will get treatment at the discretion of the surgeon. Patients who prefer not to participate will be asked for their reasons. These reasons will be recorded.

Data Management:

Database management will be done using a web-based system.

Safety: the occurrence of adverse events and subsequent knee surgeries will be queried and recorded at follow-up visits.

[figure not shown]**Figure 1: Study Flowchart**

\* Total follow up time for primary outcome in delayed APM group remains 24 months

CRF s\* = surgery / CRF c\*=conservative, CRF d\*=delayed

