### 6.2 Inclusion criteria

- 1) Patients between 45 and 70 years of age at presentation.
- 2) A meniscal tear visualized on MRI. The meniscal tear can either be isolated or combined with a partial asymptomatic Anterior Cruciate Ligament (ACL) injury or a asymptomatic degenerative ACL shown on MRI with no abnormal clinical findings (a negative Lachman test and Pivot Shift).
- 3) Mental Competence.
- 4) Willingness to comply with follow-up schedule.
- 5) Written informed consent.

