#### 8.1.2 Secondary Outcomes

1) Change in:

- General health, measured by RAND-36
- Quality of life, measured by EQ-5D5L
- Pain, measured with the VAS in rest and during weight bearing.
- Level of activity, measured by Tegner Activity Scale (TAS)
- Patient specific complaints measured by the PSC (patient specific complaints) Questionnaire
- Treatment group; number of patients initially treated conservatively, treated secondarily by APM.

We will use the EQ-5D5L to measure Quality Adjusted Life Years (QALY).

2) Productivity losses and the use of healthcare services, measured by a modified version of the Trimbos/iMTA questionnaire for Costs associated with Psychiatric Illness (TiC-P).

3) Relation between a participants expectation of treatment and their satisfaction.

4) PE, consisting of performance on physical tests (squatting with duckwalk, Thessaly test, McMurray), the range of motion, joint line tenderness and the existence of joint effusion in the knee.

5) Adverse events including:

- Minor: prolonged synovial fluid leakage from arthroscopy portals and bleeding.
- Moderate: surgical site infection, vascular and neurological damage
- Severe: septic arthritis, cardiac events, pulmonary embolism and death.

Surgical instrument malfunction will be recorded, as well as reoperations including knee arthroplasties and re-hospitalization.

6) We plan a follow up moment at 60 months to see the progression of osteoarthritis, measured with the Kellgren Lawrence Grading Scale for Osteoarthritis.

Hypotheses:

1) We assume equal improvement of physical function in both groups (a difference of < 8.8 points on IKDC 'Subjective Knee Form'). This would question the role of arthroscopic surgery in treatment of symptomatic, non-obstructive meniscal injuries in patients over 45 years old.

2) We assume with an equal improvement of function in both groups, that an initial conservative approach for this condition in older patients is much more cost-effective than APM as standard therapy.

3) We assume a lower baseline value of participants compared to the average score of the Dutch population and an equal improvement of general health in both groups (RAND-36).

4) We assume equal improvement of quality in life, measured in QALY's.

5) We assume equal improvement of pain, measured with the VAS score.

6) We assume equal improvement of activity level (Tegner Activity Score).

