7) We assume equal improvement of complaints in activities and movements found most important by patients (patient specific complaints).

8) We expect a greater reduction of joint line tenderness in the arthroscopic partial meniscectomy group shortly after therapy, compared to the physical therapy group, since part of the damaged meniscus is released. However, we expect no difference in joint line tenderness on the long term. We expect a faster reduction of joint effusion after treatment in the physical therapy group. However, we do not expect a difference between both groups after 24 months. We do not expect a significant improvement of ROM after treatment in both groups.

9) We estimate that 2/3 of surgeries can be prevented (as stated by Herrlin SV et al. (6), and therefore expect 1/3 of patients who will undergo delayed arthroscopic meniscectomy after completion of physical therapy. The possible cost reduction of this effect will be calculated in the economic analysis.

10) Patients in the physical therapy group will leave work for at least 16 sessions of 30 minutes each week, representing one working day, with the addition of travelling time. Patient in the surgery group are expected to be absent from work for one working day, the day of surgery. We therefore expect surgery to lead to more productivity losses.

11) We expect squatting to have the greatest predictive value of the different meniscal tests for detecting meniscal injuries.

12) We expect a faster development or progression of osteoarthritis after arthroscopic partial meniscectomy compared to physical therapy.

13) We expect adverse events to occur more frequently in the arthroscopic partial meniscectomy group. Patients who are subjected to delayed surgery after physical therapy has failed, remain in the physical therapy group. Therefore, we do expect adverse events to occur in the physical therapy group. Since the number in the arthroscopic partial meniscectomy group are to be expected to outnumber the number of patients with delayed surgery, we expect more adverse events in the arthroscopic partial meniscectomy group.

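### Section 10 names a pain variable other than the declared VAS and an outcome that is never measured, and parts of hypotheses 8 and 11 have no planned data

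*Protocol*

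**What the plan says.** **Pain.** Section 8.1.2 declares "Pain, measured with the VAS in rest and during weight bearing", and Section 5 has the equivalent "Pain, measured with the VAS both in rest and weight bearing". Section 10, describing the secondary GEE model, instead gives "knee pain on the question 10 of IKDC".

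**Other analysed outcomes.** The same list in Section 10 continues with "productivity losses on TiC-P, muscle strength, range of motion, squatting and adverse events". All are to be handled like the primary outcome, with time as dummies against baseline and four group-by-time terms.

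**Examination schedule.** Section 5, Follow-up: "Patients will visit the outpatient department for physical examination (3 months) and X-rays (24 months". Table 1 adds a baseline examination and none after month 3.

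**Hypotheses (Section 8.1.2).** Hypothesis 8 expects no long-term difference in joint line tenderness and, for effusion, says "we do not expect a difference between both groups after 24 months". Hypothesis 11 reads: "We expect squatting to have the greatest predictive value of the different meniscal tests for detecting meniscal injuries".

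**Population.** Section 6.2 requires "A meniscal tear visualized on MRI" of every participant.

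**The concern.** The analysis section should analyse the outcomes that the rest of the protocol declares and collects. Here it names a different pain variable and an outcome with no measurement behind it, and its model form presupposes more examinations than are scheduled. Two hypotheses also go beyond what the design can deliver.

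At stake is the reading of the secondary results. An analyst who follows Section 10 literally would report pain on something other than the declared outcome, and the protocol would hold two candidate pain variables with no rule for choosing between them. The 24-month parts of hypothesis 8 could be neither supported nor refuted, and hypothesis 11 could not be answered in the terms in which it is put.

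**Working it through.** The plan gives no figure of its own on this point, and the sample size does not enter. The check compares the sections outcome by outcome.

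**1. Pain**

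| Place in protocol | Pain variable |
|---|---|
| Summary | VAS |
| Section 5, secondary outcomes | VAS, at rest and on weight bearing |
| Section 8.1.2, outcome list | VAS, at rest and on weight bearing |
| Section 8.1.2, hypothesis 5 | VAS |
| Table 1 | VAS at baseline, 3, 6, 12 and 24 months |
| Section 10 | IKDC question 10 |

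Five places agree and one differs. Two scales at five time points make 2 x 5 = 10 declared pain scores per patient, and Section 10 names none of them. The economic evaluation uses pain intensity as an effect measure without giving an instrument, so it does not settle the matter. Sections 8.1.1 and 8.3(e) say only that item 10a stays out of the IKDC score. Nowhere does the protocol say what question 10 asks or which part of it Section 10 means.

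**2. Muscle strength**

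- Secondary outcomes in Sections 5 and 8.1.2: absent.
- Physical examination: six components (squat with duckwalk, Thessaly, McMurray, range of motion, joint line tenderness, effusion); strength is not one of them.
- Section 8.3: strength appears only as exercise content of the therapy programme, not as a measurement.
- Table 1: absent.

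Planned measurements: 0.

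**3. Physical examination**

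With time coded as dummies against baseline, the number of group-by-time terms that can be estimated equals the number of post-baseline time points.

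- IKDC: 3, 6, 12 and 24 months = 4 terms, which matches Section 10.
- Examination outcomes such as range of motion and squatting: 3 months = 1 term.

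Hypothesis 8 makes five statements:

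| Statement | Examination available |
|---|---|
| Greater early reduction of tenderness after surgery | 3 months |
| No long-term difference in tenderness | none |
| Faster reduction of effusion with physical therapy | 3 months |
| No difference in effusion after 24 months | none |
| No significant improvement in range of motion | 3 months |

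Two of the five have no planned data.

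One sentence in Section 5, Follow-up, says that all outcomes are obtained at every time point to 24 months. Read literally, it would supply the missing examinations. However, the same paragraph, the burden text after Section 6.3 and Table 1 all tie the follow-up examination to month 3. The literal reading also fails at 9 and 18 months, when the burden text limits the questionnaires to the EQ-5D-5L and TiC-P. The specific schedule is the better reading, but the sentence conflicts with it.

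**4. Hypothesis 11**

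Let se be sensitivity, sp specificity and p the prevalence of a tear among those tested.

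- PPV = se x p / [se x p + (1 - sp)(1 - p)]
- NPV = sp(1 - p) / [sp(1 - p) + (1 - se)p]

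With MRI as reference, enrolment sets p = 1:

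- PPV = se / (se + 0) = 1.00
- NPV = 0 / [0 + (1 - se)] = 0.00

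Taking assumed values of se from 0.5 to 0.9 and sp from 0.3 to 0.9 gives PPV = 1.00 and NPV = 0.00 in every case, so predictive value cannot rank the tests. Specificity needs patients without a tear, and by MRI there are 0 among the planned 320. Sensitivity remains estimable, since all 320 count as tear-positive.

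**The case against.** **The Section 10 list is illustrative.** It opens with e.g., the VAS is still collected, and a protocol may leave the full variable list to a statistical analysis plan. This stands as far as omissions go. The absence of patient specific complaints from the list is no defect, and a VAS analysis is not forbidden. It does not excuse an example that contradicts the declared outcome, or one that is never measured.

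**Question 10 might be part of the primary score.** A reader might infer that the pain conclusion would then rest on a piece of the primary outcome and be wrong. The documents do not support this. They exclude item 10a from the score but do not say which part of question 10 is meant. What they support is that it is not the declared measure.

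**Nobody would fit four terms to one follow-up visit.** Probably true, and no wrong estimate need follow. The text still prescribes a model that does not fit the schedule.

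**Hypothesis 8 states expectations, not planned tests.** Section 10 lists neither tenderness nor effusion and plans no 24-month test of them. A reader might infer that absence of a difference would be claimed without data, but nothing in the protocol says so. The short-term parts remain examinable.

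**Arthroscopy could be the reference standard for hypothesis 11.** Against arthroscopic findings, PPV would not be fixed at 100% by enrolment. That is correct. But arthroscopy is planned only for the surgical arm and delayed cases, all of them MRI-positive, and the protocol describes no such reference and no diagnostic analysis.

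**Conclusion.** The point holds for secondary outcomes only. Section 10 contradicts five other places on the pain variable and lists one outcome with no measurement. Examination outcomes have one follow-up visit against four specified terms. Two of the five statements in hypothesis 8 have no planned data. Hypothesis 11 cannot be answered as predictive value; this last result assumes MRI as the reference, the only standard that the protocol ties to enrolment.

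A reader might conclude that several secondary questions will be answered wrongly. The documents do not go that far: the declared VAS data will exist, the examination data at 3 months will exist, and the primary IKDC comparison is unaffected. The way adverse events are modelled is not part of this point.

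**What to change.** - In Section 10, replace IKDC question 10 by VAS at rest and VAS on weight bearing, keeping the IKDC item at most as supportive.
- Delete muscle strength from the list.
- State that examination outcomes are analysed as one between-group comparison at 3 months, adjusted for the baseline value and for the centre and age group already specified.
- Limit the tested part of hypothesis 8 to 3 months. Adding an examination at the existing 24-month visit would also supply effusion and tenderness data, but that is a new assessment rather than a wording change.
- Reconcile the Follow-up sentence in Section 5 on all outcomes at all time points with Table 1.
- Drop hypothesis 11, or restate it as a comparison of sensitivity among MRI-confirmed tears.

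Apart from the optional examination, this costs only wording: no new data, no change to the sample size and no effect on the primary analysis.

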#### 6.4 Sample size calculation

Sample size is based on a power of 90%, an alpha of 0.05, a standard deviation of 18 points and a non-inferiority threshold of 8 points on the IKDC (a minimal clinical important change in IKDC is 8.8) (18).

We calculated that with 10% loss to follow-up after 24 months and 25% delayed APM in the PT group, 160 patients are needed per group in this non-inferiority RCT.

This corresponds to a total of 320 patients will be included.

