## 8. METHODS

### 8.1 Primary and secondary outcome measures

#### 8.1.1 Primary outcome

Primary outcome will be change in physical function from baseline to 2 years measured by the International Knee Documentation Committee (IKDC) 'Subjective Knee Form', which has been validated for meniscal injuries (18). The IKDC is developed for knee-specific measurement of symptoms, function, and sports activities in patients with ligament and meniscal injuries. The IKDC is a self-administered questionnaire with a total of 19 questions. All items, except item 10a, are converted to a score with a maximum of 100 indicating no restrictions in daily and sports activities and the absence of symptoms. A difference of more than 8.8 points in IKDC-score is deemed clinically relevant.

In addition, we will perform an economic analysis alongside the RCT from a societal perspective and a budget impact analysis from societal, government and insurer perspective.

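### The primary GEE estimates the 24-month effect from raw change scores; adjusting for the collected baseline IKDC would estimate the same effect more precisely at little cost

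*Protocol*

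**What the plan says.** Section 8.1.1 of the protocol defines the endpoint: "Primary outcome will be change in physical function from baseline to 2 years", measured by the IKDC. Table 1 in section 8.4 (Study scheme) schedules the IKDC at baseline and at 3, 6, 12 and 24 months.

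Section 10 writes out the primary model. The IKDC is the dependent variable, "using treatment allocation (1, intervention; 0, control) and time as a key independent variables". On the time coding it says "Time will be included as a dummy variable (reference = baseline T0", and on the interactions "four interaction terms will be analyzed (T1Xgroup; T2x group; T3x group, T4x group". The effect is read from those terms: "To evaluate whether the two groups differed in change over time the interaction term of group and time (group X time) will be assessed".

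The only covariates fixed in advance are the stratification factors: "All models will be corrected for center of inclusion and age group". No covariate-by-time terms are named. Baseline IKDC is neither a covariate nor one of the candidate confounders, and nothing constrains the arms to a common baseline mean.

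Section 6.4 bases the sample size on "a standard deviation of 18 points" without saying whether this is the SD of a score or of the change.

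**The concern.** One baseline and four later IKDC visits, with four interaction terms and baseline as reference, make the baseline score a row of the outcome. (I take the four terms to be the 3, 6, 12 and 24-month IKDC visits, although their labels differ from those in Table 1.) With a free group term at baseline, the 24-month interaction is the raw difference in mean change, and any chance baseline imbalance is subtracted in full. A baseline-adjusted model subtracts only the part that the correlation supports, so its interval is narrower.

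The correction for centre and age group does not make up for this. Both are constant over time, so as main effects they cancel out of within-patient change.

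In a non-inferiority trial the width of the interval decides whether the margin is excluded, so precision bears directly on the conclusion.

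**Working it through.** **Inputs from the protocol.** Margin 8, SD 18, power 90%, alpha 0.05, 10% loss, 25% delayed APM and 160 per group (section 6.4); two-tailed testing (section 10), hence one-sided 0.025 for non-inferiority. **Assumed:** ρ, taken as 0.3, 0.5 and 0.7.

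**1. The plan's own figure.** n = 2(1.960 + 1.282)² × 18² / 8² = 106.4, so 107 per arm. Then 107 / (0.90 × 0.75) = 159, against the stated 160. Conversely, 160 × 0.675 = 108 per arm is the number on which the stated power rests.

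**2. What the interaction estimates.** In simulated complete data (320 patients, five visits, nine centres, two age groups), the 24-month group-by-time coefficient equalled the raw difference in mean change to about 1e-14.

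**3. What centre and age add.** Entered as main effects (15 simulated trials per setting, ρ = 0.5):

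| Missing data | Working correlation | Largest shift in estimate (points) | SE without → with centre and age |
|---|---|---|---|
| none | either | about 1e-14 | 2.057 → 2.057 |
| 10% | exchangeable | 0.13 | 2.128 → 2.128 |
| 10% | independence | 0.48 | 2.166 → 2.161 |
| 32.5% | exchangeable | 0.16 | 2.342 → 2.338 |
| 32.5% | independence | 0.73 | 2.515 → 2.482 |

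The estimate can move when data are missing, but the SE falls by 1.3% at most.

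**4. What baseline adjustment adds.** With a common score SD s:
- variance of change = 2s²(1 − ρ);
- variance after adjustment = s²(1 − ρ²);
- ratio = (1 + ρ)/2 = 0.65, 0.75, 0.85.

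With unequal SDs s₁ (baseline) and s₂ (24 months), the change score's excess variance is (s₁ − ρs₂)², which is never negative. In large samples adjustment therefore does not lose.

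Mean SEs over 60 simulated trials, planned model against adjustment for baseline, centre and age, were 2.40 and 1.95 (ρ = 0.3), 2.03 and 1.77 (0.5), 1.59 and 1.46 (0.7). Squared ratios are 0.66, 0.76 and 0.84, in line with the formula.

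**5. If 18 is the SD of change.** The adjusted SD is 18 × √((1 + ρ)/2) = 14.5, 15.6, 16.6. Evaluable patients per arm for 90% power fall from 107 to 70, 80, 91. The plan meets its power without adjustment.

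**6. If 18 is the SD of a score.** Power = Φ(8 / (SD × √(2/n)) − 1.96), where SD is 18√(2(1 − ρ)) for change and 18√(1 − ρ²) after adjustment.

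| ρ | SD of change | SD adjusted | Power at 108 per arm: change / adjusted |
|---|---|---|---|
| 0.3 | 21.3 | 17.2 | 78.8% / 92.8% |
| 0.5 | 18.0 | 15.6 | 90.4% / 96.5% |
| 0.7 | 13.9 | 12.9 | 98.8% / 99.6% |

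Sections 5 and 7 place delayed-APM patients in the intention-to-treat analysis, and section 5 says the sample size is for that analysis. With 10% loss alone, n = 160 × 0.90 = 144 per arm, and the ρ = 0.3 comparison becomes 89.0% against 97.7%.

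**The case against.** The strongest reply is that this is a preference. The endpoint is declared as a change, the planned term estimates exactly that, and the fuller specification could sit in an SAP that is not shown; section 10 also promises that a statistician will be consulted. What stands is that nothing here is invalid: under randomization the interaction is unbiased, and the sample size reproduces. What does not stand is deferral. Section 10 fixes the model term by term, and with equal expected baselines the adjusted model estimates the same group difference.

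Three stronger readings are tempting and are not supported:

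- A reader might infer that centre and age can never move the estimate. That is exact only for complete, unweighted data with main effects. Section 10 foresees missing data, imputation and a weighted GEE, and its wording does not exclude covariate-by-time terms. The supported statement is that main effects add almost no precision.
- A reader might infer that the trial has only 79% power. That needs an assumed ρ of 0.3, an SD of 18 that refers to a score, and 108 per arm. At 144 per arm it is 89.0%; at ρ of 0.5 or 0.7 the planned model reaches 90% even at 108. Where there is a shortfall, it comes from the unlabelled SD combined with a low ρ.
- A reader might treat a GEE with a common baseline mean as interchangeable with baseline adjustment. This depends on the working correlation, which section 10 does not name.

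**Conclusion.** The point holds as a loss of precision, not as bias or a faulty sample size. The written primary model gives the unadjusted difference in change. Baseline adjustment would reduce its variance by 35%, 25% or 15% at assumed ρ of 0.3, 0.5 or 0.7, and the gain vanishes as ρ approaches 1.

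Whether power is at risk depends on what the SD of 18 measures. If it is the SD of change, the stated 90% is met and the gain is spare margin. If it is the SD of a score, the planned model falls short at 108 per arm when ρ is below 0.5; at 144 per arm and ρ = 0.3 it is about one percentage point short. These figures assume equal score variances at baseline and 24 months, a true difference of zero, and the normal approximation.

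**What to change.** In section 10, model post-baseline IKDC (3, 6, 12 and 24 months) on group, time, group by time, baseline IKDC with baseline by time, centre and age group. Read the 24-month group contrast from that model, and do the same for other repeated outcomes that have a baseline value. In section 6.4, state whether 18 is the SD of a score or of the change.

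If a common-baseline model is preferred, name a working correlation other than independence. Under independence that model reduces, covariates apart, to the unadjusted 24-month difference, with variance proportional to s² against 2s²(1 − ρ) for change, so it is less precise than change scores once ρ exceeds 0.5. In simulation at 144 per arm and ρ = 0.7 its SD was 2.16, against 1.62 for change scores; it matched baseline adjustment only with an exchangeable structure.

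The cost is slightly more modelling, on data already scheduled, and one small procedural point. Section 8.4 (Study scheme) lists the baseline questionnaire after assignment, and section 8.2 describes an open trial, so the questionnaire should be completed before the allocation is disclosed.
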